### Eligibility criteria

2.2

#### Inclusion criteria for patients

2.2.1

Laboratory-confirmed influenza virus infection via nucleic acid testing [reverse transcription polymerase chain reaction (RT-PCR)] or rapid antigen testing, adhering to China’s *Diagnosis and Treatment Protocol for Influenza*;All age groups;Written consent obtained from patients: (a) patients with full civil capacity (more than 18 years); (b) Legal guardians for minors (less than 18 years), incapacitated adults, or patients with cognitive impairment.

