**Ethics and dissemination:**

This study was approved by the Institutional Review Board of Yangzhou University Hospital (IRB No. YKL08-002). Written informed consent was obtained from all participants. The results of this study will be disseminated in the form of a conference in the Jiangsu Province area, which will facilitate the translation of clinical research results and provide a powerful decision-making tool for the precise prevention and control of severe influenza.

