#### Phase I: model development and internal validation

2.3.1

This phase utilizes retrospective EHRs from 87 hospitals (Table 1) in Jiangsu Province (from January 2019 to December 2024), encompassing four key data categories:

Demographics: age, sex, vaccination history, and comorbidities.Clinical symptoms: fever duration, cough frequency, dyspnea severity, and other symptoms detailed (Table 2).Laboratory/imaging data: viral subtype (confirmed via RT-PCR), blood cell counts, and chest X-ray/computed tomography (CT) findings.Outcomes: severe influenza progression and mortality, defined as intensive care unit (ICU) admission or mechanical ventilation.

**Table 1 tab1:** Datasets distribution.

City	Hospitals
Nanjing	Jiangsu Provincial People’s Hospital, General Hospital of the Eastern Theater Command, Nanjing Drum Tower Hospital, Jiangsu Provincial Hospital of Traditional Chinese Medicine, Zhongda Hospital Affiliated to Southeast University, Nanjing First Hospital, The Second Affiliated Hospital of Nanjing Medical University, Nanjing Hospital of Traditional Chinese Medicine
Wuxi	Wuxi People’s Hospital, The Affiliated Hospital of Jiangnan University, Wuxi Hospital of Traditional Chinese Medicine
Xuzhou	The Affiliated Hospital of Xuzhou Medical University, Xuzhou Central Hospital, Xuzhou First People’s Hospital, Xuzhou Mining Group General Hospital, Xuzhou Hospital of Traditional Chinese Medicine
Changzhou	Changzhou First People’s Hospital, Changzhou Hospital of Traditional Chinese Medicine, The Third Affiliated Hospital of Soochow University (Changzhou Second People’s Hospital)
Suzhou	The First Affiliated Hospital of Soochow University, The Second Affiliated Hospital of Soochow University, Suzhou Municipal Hospital, Suzhou Hospital of Traditional Chinese Medicine
Nantong	The Affiliated Hospital of Nantong University, Nantong First People’s Hospital, Nantong Hospital of Traditional Chinese Medicine
Lianyungang	Lianyungang First People’s Hospital, Lianyungang Hospital of Traditional Chinese Medicine, Lianyungang Second People’s Hospital
Huai’an	Huai’an First People’s Hospital, Huai’an Second People’s Hospital, Huai’an Hospital of Traditional Chinese Medicine
Yancheng	Yancheng First People’s Hospital, Yancheng Hospital of Traditional Chinese Medicine, Yancheng Third People’s Hospital
Yangzhou	Subei People’s Hospital, Yangzhou First People’s Hospital, Yangzhou Hospital of Traditional Chinese Medicine

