#### Final allocation

2.5.3

The study will enroll a total of 348 patients, comprising both retrospective cohorts (historical data from 2019 to 2024) and prospective cohorts (real-time data from the 2025 influenza season). Clinician participation includes 218 practitioners, stratified by hospital tier (urban vs. rural) and seniority level (resident, attending, or chief physician) to ensure balanced representation of clinical expertise and institutional resource variability. This allocation strategy optimizes statistical power while reflecting real-world healthcare diversity, supporting robust validation of the AI model across heterogeneous settings.

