#### Data collection timeline

2.7.2

The study’s data collection is structured into two distinct phases: retrospective (Phases I–II) and prospective (Phases III–V).

During the retrospective phase, EHRs data spanning 2019 to 2024 will be extracted from all 87 participating hospitals via institution-specific application programming interfaces (APIs), with completion targeted within 6 months to ensure timely progression to subsequent stages.

In the prospective phase, real-time data collection will occur throughout the 2025 influenza season, capturing clinical, diagnostic, and outcome variables as they emerge. These data will be synchronized daily to a centralized, secure database to maintain continuity and enable immediate analysis.

This phased approach balances historical insights with dynamic, real-world validation, ensuring comprehensive evaluation of the AI model across diverse temporal and operational contexts.

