## Ethics and dissemination

3

This study received ethical approval from the Ethics Committee of the Affiliated Hospital of Yangzhou University (Approval No. 2024-10-02). Annual renewals of ethical approval will be submitted to ensure ongoing compliance with evolving regulatory and ethical standards. Informed consent was obtained from all participants: patients or their legal guardians (for minors or incapacitated adults) provided written consent for anonymized data collection and analysis, while clinicians signed agreements acknowledging their roles in diagnosis and model interaction, with the explicit right to withdraw at any time. To safeguard privacy, all patient identifiers were replaced with unique study codes, and anonymized data were stored on the OSF platform (osf.io/ayj75), accessible only to authorized researchers via two-factor authentication. These measures align with international data protection standards and China’s Data Security Law, ensuring ethical integrity and participant confidentiality throughout the study.

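### The written-consent criterion has no phase limit, so as written it selectively depletes the retrospective 2019–2024 data of fatal cases and conflicts with the planned bulk record extraction

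*Protocol article*

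**What the plan says.** - **Entry rule.** Section 2.2.1 of the protocol article has one list of patient inclusion criteria for the whole study. It includes "Written consent obtained from patients: (a) patients with full civil capacity (more than 18 years); (b) Legal guardians for minors", and the item goes on to cover incapacitated adults and patients with cognitive impairment. Nothing limits it to the prospective phases.
- **Who counts as enrolled.** Section 2.5.3: "The study will enroll a total of 348 patients, comprising both retrospective cohorts (historical data from 2019 to 2024) and prospective cohorts".
- **Consent reported for everyone.** The abstract (Ethics and dissemination) states: "Written informed consent was obtained from all participants". Section 3 repeats this and ties it to use of the data: "patients or their legal guardians (for minors or incapacitated adults) provided written consent for anonymized data collection and analysis".
- **Source of the model-building data.** Section 2.3.1 uses "retrospective EHRs from 87 hospitals (Table 1) in Jiangsu Province (from January 2019 to December 2024". Section 2.7.2 places Phases I and II in the retrospective part and says "EHRs data spanning 2019 to 2024 will be extracted from all 87 participating hospitals", through hospital interfaces, with completion targeted within 6 months.
- **Role of death.** Section 2.3.1 lists "Outcomes: severe influenza progression and mortality, defined as intensive care unit (ICU) admission or mechanical ventilation". Table 2 lists mortality as an outcome item, and section 2.4.5 has the adjudication panel verify it as one of the endpoints.

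**The concern.** An adult who died before consent was sought cannot sign, and the proxies listed are guardians of living patients. A survivor who has moved or cannot be traced is also lost. If the rule is applied to historical records, inclusion therefore depends in part on the outcome that the study records and adjudicates.

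The model is trained and tuned in Phase I and compared with clinicians in Phase II on these records. In Phase V it runs on newly admitted patients, whose later death does not prevent entry. The case mix at development would then differ from the case mix at use, and the difference would be concentrated in the most severe patients. The Introduction gives reduction of influenza mortality as the purpose of the work, so this is the group the tool can least afford to under-represent.

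**Working it through.** The plan states no figure on this point, so there is none to reproduce. The check has a textual part and an illustration.

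**1. Does anything exempt the retrospective cohort?**

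| Question | What the article says |
|---|---|
| Is the consent criterion limited by phase? | No (2.2.1) |
| Are the 2019–2024 patients outside enrolment? | No, they are among the 348 (2.5.3) |
| Is consent claimed only for prospective patients? | No, for all participants (abstract, section 3) |
| Is there a waiver or opt-out for historical records? | None stated |
| Is there a route for deceased patients? | None stated |
| Is there a step for contacting past patients? | None; extraction is through hospital interfaces (2.7.2) |

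Two readings remain. Either consent is required for the historical records, and deaths that occurred before consent was sought drop out. Or the records enter without individual consent, and the abstract, 2.2.1 and section 3 are wrong for Phases I–II. Each reading requires a correction.

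**2. How large could the depletion be?**

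Two inputs are needed, and the documents give neither:
- *m*, the fatality among severe cases (assumed 5%, 10%, 20% or 40%);
- *q*, the share of those deaths without consent (assumed 50% or 100%).

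Formulas:
- share of severe cases lost = *m* × *q*
- fatality among the severe cases that remain = *m*(1 − *q*) / (1 − *mq*)

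| *m* | lost, *q* = 50% | lost, *q* = 100% | remaining fatality, *q* = 50% | remaining fatality, *q* = 100% |
|---|---|---|---|---|
| 5% | 2.5% | 5% | 2.6% | 0% |
| 10% | 5% | 10% | 5.3% | 0% |
| 20% | 10% | 20% | 11.1% | 0% |
| 40% | 20% | 40% | 25% | 0% |

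Worked line for *m* = 20%, *q* = 50%: lost = 0.20 × 0.50 = 0.10; remaining fatality = 0.10 / 0.90 = 11.1%. The 20% matches the general mortality figure in the Introduction, borrowed here only as an assumption.

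Suppose also that 10% of patients are severe and that every non-severe patient enters (both assumptions). With *m* = 20%, the observed severe share falls to 0.10 × 0.90 / (1 − 0.10 × 0.10) = 0.09 / 0.99 = 9.1% for *q* = 50%, and to 0.08 / 0.98 = 8.2% for *q* = 100%.

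**3. Which way does the AUC move?**

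Write the AUC as a weighted mean over the severe cases, with A_d for those who died and A_s for severe survivors. Full AUC minus consented AUC = (*m* − *m′*)(A_d − A_s), where *m′* is the remaining fatality. Since *m′* is below *m*, the sign is that of A_d − A_s, which the documents do not give. If deaths are easier to score, for example A_d = 0.95 and A_s = 0.82 (assumed) with *m* = 20%, the AUC goes from 0.846 to 0.834 (*q* = 50%) or 0.820 (*q* = 100%). If deaths are harder to score, it moves the other way.

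**The case against.** **The date of consent is unknown.** A reader might infer from the approval number in section 3 (2024-10-02) that consent was first sought in late 2024, so that anyone who died earlier could not be asked. The article does not say that the number is a date, and the abstract cites a different approval number. Section 2.1 calls the study a continuation of a 2019 investigation, and section 3 reports consent in the past tense. Consent at admission or in the earlier study would let patients who later died enter. This objection stands against any claim that all deaths are lost. It does not rescue the text, because nothing says that earlier consent covers these records or this use.

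**The data are not survivors only.** A reader might infer this too. A guardian can consent for an incapacitated adult before death, and severe survivors who were in ICU or ventilated remain. The supported word is depletion.

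**The wording may be boilerplate.** Section 2.1.1 requires anonymous data-sharing programmes and section 2.7.2 describes automated extraction, so the team may never have meant to seek consent for old records. A condensed article may also leave the consent basis to the full protocol and ethics file. That would excuse silence. Here the article states a rule and states that it was met for everyone, which cannot easily be squared with the extraction it describes.

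**The randomised comparison is unaffected.** Depleted training data could weaken the tool, but would not bias the Phase IV contrast between randomised clinicians, and Phase V could reveal poor transfer. This stands: the point concerns the Phase I–II data and what is claimed from them.

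**Conclusion.** The point holds as a defect in the stated entry rule. Consent from the patient or a guardian is required without phase limit, the retrospective cohort is counted as enrolled, consent is claimed for all, and no waiver or route for the deceased is given. Applied as written, this makes entry to the Phase I–II data depend partly on survival and reachability, and it contradicts the extraction procedure.

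The documents do not fix the size of the effect. The 2.5–40% range for severe cases lost rests wholly on the assumed fatality and the assumed share of deaths without consent. If unconsented deaths are removed and other patients are not, the fatal and severe shares fall; the sign of any AUC bias is open.

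A reader might reach a much larger loss by setting the Introduction's 20% mortality against an assumed 30–40% severe share (20/40 = 50%, 20/30 = 67%). The documents do not support that. The 20% is a background statement about influenza in general, the severe share is invented, and the result needs every death to be unconsented and every death to count as severe. The last is itself unsettled: section 2.3.1 defines the outcome by ICU admission or ventilation and Table 2 lists mortality separately, while section 2.4.5 includes it among the verified endpoints.

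**What to change.** 1. In section 2.2.1, limit the written-consent criterion to prospectively enrolled patients.
2. For the de-identified 2019–2024 records, obtain an ethics-approved waiver of individual consent or an opt-out, and include every otherwise eligible record, deaths included.
3. Reconcile the abstract's ethics statement and sections 2.2.1, 2.5.3, 2.7.2 and 3, so that each gives the same consent basis for the retrospective and the prospective patients.
4. If a waiver is not granted, state that the retrospective data are depleted of deaths and limit the mortality-related claims from Phases I–II.

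The cost is an ethics amendment and rewording, with no extra patients or procedures. It should be settled before the training data are fixed, because imputation cannot restore patients who were never included.

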#### Exclusion criteria for patients

2.2.2

Co-infection with other respiratory pathogens confirmed by multiplex polymerase chain reaction (PCR);Critical illness unrelated to influenza at enrollment;Incomplete baseline data (such as missing symptom onset date, laboratory results).

#### Inclusion criteria for clinicians

2.2.3

less than 5 years of clinical experience in influenza diagnosis or participation in national-level influenza research projects;Willingness to complete protocol-mandated tasks, including dual-round diagnosis (baseline vs. model-assisted) and post-study interviews;Currently practicing in a tertiary general hospital in Jiangsu Province.

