#### Phase II: external validation-comparative study

2.3.2

The goal of the second phase of the task was to comparatively confirm the diagnostic accuracy of the additional diagnostic assessment using the AI models built in the first phase to assist clinicians in diagnostic assessment. We categorised clinicians into residents, attending physicians and chief physicians according to their experience level. We asked clinicians in the control group to independently judge these influenza cases without the assistance of the AI model; while clinicians in the experimental group did the diagnostic assessment of these influenza cases with the assistance of the AI model. Under this comparison, the metrics of AUC, sensitivity, specificity, and diagnostic consumption time are what are used to initially evaluate the performance of the AI model. Imagine the exciting news that an AI model-assisted clinician can complete a diagnostic assessment with 95% accuracy in just 10 minutes. This dual assessment framework quantifies the added value of AI models in the real world.

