#### Phase IV: randomized controlled trial

2.3.4

This phase is a pragmatic randomised controlled design to assess the effectiveness of AI-assisted diagnosis in the real world. Clinicians will be assigned in a 1:1 ratio to either the control group (using standard clinical assessment protocols) or the AI model-assisted group. Allocation will be by block group randomisation, stratified by hospital level (urban vs. rural) and clinician experience level (resident, attending, chief) to ensure balanced representation in key subgroups.

The control group will rely exclusively on routine diagnostic workflows, while the model-assisted group will integrate AI outputs into their decision-making process and retain full authority to accept or reject recommendations. The primary outcome is the between-group AUC difference, with a ΔAUC greater than 0.15 defined as clinically significant, which is consistent with the U.S. Food and Drug Administration’s (FDA) benchmarks for diagnostic tools based on artificial intelligence or machine learning (AI/ML). The design simulates real-world clinical practice and quantifies the added value of AI in improving diagnostic accuracy while preserving clinician autonomy.

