#### Subgroup analyses

2.4.3

Predefined subgroup analyses will assess heterogeneity in model performance across key variables to evaluate the impact of local healthcare infrastructure and influenza epidemiology.

patient characteristics: age (infants, children, adults, older adults), comorbidities (cardiovascular disease, diabetes), and vaccination status (yes, no);clinician factors: experience level (resident, attending, chief physician);hospital resource tier: urban or rural facilities;geographic variation: northern or southern regions of Jiangsu Province.

These analyses aim to identify subgroups where the model excels or underperforms, informing targeted clinical deployment. Statistical adjustments, such as Bonferroni correction for multiple comparisons and multivariable regression for confounders, will ensure robust interpretation of subgroup differences.

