#### Sample size derivation

2.5.2

The sample size calculation began with an initial estimate of 145 patients per group (290 total), derived from a power analysis targeting a clinically significant ΔAUC of 0.15 (*α* = 0.05, *β* = 0.95). To account for potential 20% attrition due to incomplete data or participant dropout, the final patient sample was adjusted to 174 per group (348 total). For clinicians, a minimum of 218 participants (109 per group) was required to ensure balanced representation across experience levels (resident, attending, chief) while addressing hospital-level clustering effects, as recommended by methodology for cluster-randomized trials (35). This dual-tiered approach balances statistical precision with pragmatic considerations, ensuring robust evaluation of the AI model’s impact in diverse clinical environments.

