#### Randomization and allocation

2.6.1

A computer-generated randomization sequence will be created using the blockrand package in R, stratified by hospital tier (urban vs. rural) and clinician experience level (resident, attending, or chief physician). This approach ensures balanced allocation across subgroups, minimizing confounding effects from institutional resources or practitioner expertise. Participants will be assigned to either the control group (standard clinical diagnosis) or the model-assisted group (AI-supported diagnosis) at a 1:1 allocation ratio. The randomization sequence will be concealed in sequentially numbered, opaque envelopes managed by an independent statistician to prevent selection bias, ensuring equitable distribution of participants and maintaining trial integrity.

To ensure unbiased group assignment, an independent statistician uninvolved in recruitment or data analysis will prepare opaque, sequentially numbered envelopes containing group allocations (control or model-assisted). These sealed envelopes will be securely stored and only opened sequentially by a dedicated study coordinator after clinicians complete baseline assessments. This procedure rigorously prevents selection bias by concealing allocation details until the point of intervention assignment, thereby safeguarding the randomization integrity and ensuring equitable distribution of participants across study groups.

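### The 5-year ceiling on clinicians' influenza experience conflicts with the resident, attending and chief strata used for randomisation, sample size and subgroups

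*Protocol article*

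**What the plan says.** Section 2.2.3 (Inclusion criteria for clinicians) gives the only experience requirement: "less than 5 years of clinical experience in influenza diagnosis or participation in national-level influenza research projects". The other two conditions are willingness to do the study tasks and current practice in a tertiary general hospital in Jiangsu. No other section relaxes or restates the limit.

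The rest of the design works with three ranks, ordered by experience:

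- Phase II (2.3.2): "We categorised clinicians into residents, attending physicians and chief physicians according to their experience level".
- Phase IV (2.3.4): "Clinicians will be assigned in a 1:1 ratio", with allocation "stratified by hospital level (urban vs. rural) and clinician experience level (resident, attending, chief) to ensure balanced representation in key subgroups".
- Randomization and allocation (2.6.1): "stratified by hospital tier (urban vs. rural) and clinician experience level (resident, attending, or chief physician".
- Sample size derivation (2.5.2): a minimum of 218 clinicians, 109 per group, "was required to ensure balanced representation across experience levels (resident, attending, chief". Final allocation (2.5.3) also stratifies the 218 by seniority.
- Subgroup analyses (2.4.3, repeated in 2.8.3): "experience level (resident, attending, chief physician".

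**The concern.** The eligibility rule and the strata describe different populations. An upper limit on experience shuts the most experienced clinicians out of the ordinary route into the trial. Three parts of the plan nevertheless depend on the most senior rank being present in numbers: the stratified randomisation, the justification of the clinician sample, and the subgroup analysis by experience.

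Three things are at stake. The chief stratum may be small. Even if it fills, many of its members would have entered because of a national research role, and they need not represent chief physicians in general. And the abstract sets the model against usual clinical assessment, whereas a sample tilted towards clinicians with under 5 years of influenza experience supports a narrower statement. Analysis cannot recover a rank that was never enrolled, so this has to be settled at eligibility.

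**Working it through.** **1. Setting the sections side by side.**

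| Clinician | Experience route (literal text) | Research route |
|---|---|---|
| Under 5 years of influenza diagnosis, any rank | open | open if they have such a role |
| 5 years or more, any rank | closed | open if they have such a role |

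Section 2.3.2 says the ranks follow experience, so the closed cell falls mainly on chiefs and on longer-serving attendings. If the limit was meant as a minimum of 5 years, the closed cell moves to clinicians with under 5 years, and residents become the rank that depends on the research route. The conflict with a three-rank design exists under both readings, but it hits a different rank in each.

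**2. The plan's own figure.** The article gives no formula, quota per rank, cluster size or intracluster correlation for 218, so 218 can be neither reproduced nor refuted here. Only its stated reason, balance across the three ranks, is used below.

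**3. What balance would require.** Inputs: 218 clinicians and 109 per group (2.5.2), 3 ranks and 2 hospital tiers (2.3.4), 87 hospitals (2.1). Assumption: balance means equal thirds and equal tiers, which the article does not state.

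- Chiefs: 218 / 3 = 72.7, about 73. Per arm: 109 / 3 = 36.3, about 36.
- Chiefs per tier: 218 / 6 = 36.3, about 36. Per tier and arm: 109 / 6 = 18.2, about 18.
- Chiefs per hospital: 73 / 87 = 0.84.

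**4. Whether 73 chiefs can be found.** Let q be the share of chiefs who qualify. If every chief has 5 or more years of influenza-diagnosis experience, q is the share with national-level research participation; chiefs below the limit would raise it. The article does not give q, so a range is shown. Chiefs to screen = 73 / q; per hospital = (73 / q) / 87.

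| q (assumed) | Chiefs to screen | Per hospital |
|---|---|---|
| 2% | 3,650 | 42.0 |
| 5% | 1,460 | 16.8 |
| 10% | 730 | 8.4 |
| 20% | 365 | 4.2 |
| 50% | 146 | 1.7 |

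At the low end the stratum could hardly be filled. At the high end it could, but with a selected group.

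**The case against.** **The chief stratum need not be nearly empty.** A reader might infer that it would be. The document does not show this. The criterion is an alternative, so research-active chiefs qualify. It limits years of influenza diagnosis, not years in practice. Less than one chief per hospital is needed under equal thirds, and neither years by rank nor q is given. This objection stands, so the point is a contradiction and a risk, not a demonstrated absence. The reply is limited: participating hospitals must have had at least 100 laboratory-confirmed influenza patients in 2021 to 2023 (2.1.1), so long-serving clinicians there could plausibly exceed 5 years.

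**It may be a wording slip.** Pairing a ceiling on experience with national-level research, which reads as a mark of expertise, suggests that a minimum was intended. That is quite possible. It does not remove the conflict, but it changes which rank is affected, so no direction of enrichment should be taken as certain. Nor is a nearly empty rank shown under the second reading, because the research route is open to residents too.

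**The randomised comparison is sound.** A reader might infer that the trial becomes a contest between AI and inexperienced clinicians, or that the AUC difference is biased. The document does not support that. Phase IV compares assisted with unassisted clinicians, allocated 1:1 within rank and hospital tier, and the same eligibility rule binds both arms. The objection stands; the harm is to generalisability and to the rank-specific analysis.

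**Reader mix could carry the result past 0.15.** This too might be inferred, but it depends entirely on assumed gains. Purely as illustration, compare equal ranks with an assumed 70/25/5 mix of residents, attendings and chiefs:

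- Gains of 0.20, 0.15 and 0.08: (0.20 + 0.15 + 0.08) / 3 = 0.143, against 0.140 + 0.0375 + 0.004 = 0.182.
- Gains of 0.12, 0.15 and 0.18: 0.45 / 3 = 0.150, against 0.084 + 0.0375 + 0.009 = 0.131.
- Equal gains: no change.

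The article gives no gains by rank and no expected mix, so neither the direction nor the size of any shift is known.

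**Conclusion.** The contradiction is on the page and should be resolved. Read literally, section 2.2.3 leaves chief physicians and attendings with 5 or more years of influenza-diagnosis experience only the research route, while randomisation, the reason given for 218 clinicians and the experience subgroup all need a chief level. It threatens the size and representativeness of that stratum and narrows what can be concluded about clinicians in general. It does not bias the comparison between arms.

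The size of the shortfall is unknown. The target of about 73 chiefs assumes equal thirds, and feasibility turns on an unreported share of eligible chiefs. That the rule conflicts with the strata rests on the text alone, together with the article's own ordering of rank by experience.

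**What to change.** In section 2.2.3, confirm which direction of the 5-year limit is intended, then make eligibility and strata agree. Two ways are open:

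- Preferred: define eligibility by current rank (resident, attending, chief) with direct care of influenza patients and no years-of-experience limit. The strata in 2.3.4 and 2.6.1, the rationale in 2.5.2 and 2.5.3, and the subgroups in 2.4.3 and 2.8.3 can then stay as they are.
- If a limit is kept as a deliberate choice, remove the rank it excludes from the strata and subgroup analyses, revise the balance rationale for 218, and restrict the conclusion to the clinicians admitted.

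The cost is one eligibility sentence if clinicians have not yet been recruited. The ethics section reports consent and clinician agreements in the past tense, so if enrolment has begun the change is a formal amendment, and the ranks and experience of those already enrolled should be reported. With all ranks represented the observed AUC difference may change, possibly becoming less favourable to the model.
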